#### Cognitive and emotional self-regulation

For children over 5 years old, the Skills and Difficulties Questionnaire (SDQ) will be used to assess cognitive and emotional self-regulation, behavior problems, emotional symptoms, hyperactivity/attention deficit, peer relationships, prosocial behavior, and externalizing and internalizing problems. International studies have shown that the SDQ has sufficient validity as a detection and screening tool for children and adolescents [33]. In Spain, normative values for the Spanish version of the SDQ have been available since 2014 [34]. Therefore, the SDQ is a valuable tool for measuring and detecting emotional and behavioral problems in children. In addition, a standardized Child Self-Regulation and Behavior Questionnaire (CSBQ) will be utilized to assess cognitive and emotional self-regulation, sociability, prosocial behavior, and the presence of externalizing and internalizing problems in children. The questionnaire will be completed by the participants’ parent(s)/guardian(s) and will be collected through Google Forms.

#### The Youth Activity Profile-Spain (YAP-S) questionnaire

The following data will be collected using a standardized questionnaire through Google forms, completed by the participants’ parent(s) or guardian(s), to assess the children’s physical activity levels [35]. The questionnaire has been adapted to meet the needs of preschoolers aged 4 to 5 years old and includes additional questions, such as “Does your child enjoy participating in basic motor competencies classes offered at school?” “How many sports and/or cultural activities does your child participate in per week?” “Does your child have a television in their room?” “Is there a limit on the time your child is allowed to spend using digital devices, such as television, video games, computers, and phones?” “Are there any green areas or sports centers in your neighborhood? and Has a doctor recommended physical activity for your child in the past 12 months?”.

#### Mediterranean Diet—Children’s Eating Habits Questionnaire

The following dietary information will be recorded in a standardized questionnaire through Google forms, completed by the child’s parent(s) or guardian(s) [36]. For beneficial components (for example, vegetables, legumes, fruits, cereals, fish, dairy products, olive oil), the frequency scoring is higher than for components considered less beneficial (meat, fast food, confectionery).

#### Sociodemographic questionnaire

Variables measured by self-report will be collected via a standardized questionnaire completed by the participants’ parent(s)/guardian(s) using Google forms, such as child’s information (e.g., school, gender, age, place of birth, ethnicity, language spoken at home, and languages spoken by the child), and parent(s)/guardian(s) information (e.g., place of birth, age, highest education level, highest professional qualifications, employment status, job position, and monthly income, and household location and neighborhood).

### Participant timeline {13}

The outcome measures will be assessed at four time points [at baseline, at week 0 (T0), week 12 (T1), and week 24 (T2)], and the parent(s)/guardian(s) will be reminded to complete the questionnaires within a week. If needed, the research assistants will schedule an interview to complete the questionnaires on a tablet (Fig. 3).

**Fig. 3 Fig3:**
[figure not shown]
Schedule illustrating enrolment and interventions (SPIRIT figure) of the “3, 2, 1 Move on Study”. T, time-point. According to SPIRIT 2013 statement. Double asterisks (**) indicate the following: a random subsample of participants (40 subjects in each group, *n* = 80)

### Sample size {14}

There was some evidence to suggest that physical activity interventions [37] led to an improvement in the proportion of children who engaged in MVPA during scholar day (odds ratio (OR) 2.74, 95% confidence interval (CI), 2.01 to 3.75). Study parameters are as follows: alpha = 0.05, power = 0.80, delta =  − 1.37 (OR difference with control group). After adjustment for an estimated 10% estimated dropout rate (a similar rate has been observed in previous systematic reviews [38]), 42 participants per group will be needed for sufficient power (difference in the mean daily MVPA between groups of ± 5 min) at follow-up.

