## Outcomes {12}

### Primary outcome

The primary outcome will be mean minutes of moderate-to-vigorous physical activity (MVPA) per day assessed using GENEActiv accelerometers. The study will be able to detect a difference in the mean daily MVPA between intervention and routine care of ± 5 min at follow-up.

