## Statistical methods

### Statistical methods for primary and secondary outcomes {20a}

The study will adhere to the intention-to-treat principle and use the baseline observation carried forward imputation method, where missing data will be replaced by baseline values [39]. The final analysis population will be described and any differences from the enrolled population will be reported. Participants who drop out of the study may still be included in the analysis, although their data will provide less information and lower the estimated effects variance. Adherence will be measured as the number of completed sessions divided by the total number of sessions, expressed as a percentage. The first step of the analysis will be to calculate descriptive statistics for the overall sample and between groups. Since this is an experimental design with primary and secondary outcomes measured at three timepoints - baseline (t0 = week 0), post-intervention (t1 = week 12), and after a 12-week follow-up period (t2 = week 24) - for the two study groups (exercise and routine care), a comparative analysis between the measurements will determine the differences. A linear mixed model with repeated observations will be used for these comparisons, when appropriate, for each dependent variable. Subsequently, multivariate analysis will be carried out, and the autocorrelation between repeated measures will be taken into account. We will use longitudinal analysis methods, such as a generalized estimating equation approach, to control the differences among measurements at baseline and to incorporate incomplete observations into this analysis. Pearson correlations will be calculated between the maximal values of the primary and secondary outcomes. All analyses will be 2-sided and a significance level of *α* ≤ 0.05 will be used for the primary analysis.

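### The stated power for a ±5 min/day difference in MVPA rests on an odds ratio for a proportion and an undefined delta, so it is unsupported

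*Protocol article*

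**What the plan says.** The Primary outcome section defines a continuous endpoint: "The primary outcome will be mean minutes of moderate-to-vigorous physical activity (MVPA) per day", measured by accelerometer. It adds that "The study will be able to detect a difference in the mean daily MVPA between intervention and routine care" of ±5 min at follow-up.

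The Sample size section {14} starts from earlier evidence that activity interventions "led to an improvement in the proportion of children who engaged in MVPA during scholar day", quoted as "odds ratio (OR) 2.74, 95% confidence interval (CI), 2.01 to 3.75". It sets "alpha = 0.05, power = 0.80" and a delta of minus 1.37, described as "OR difference with control group". After a 10% dropout allowance it concludes that "42 participants per group will be needed for sufficient power", again for ±5 min of mean daily MVPA.

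The statistical methods section {20a} makes the tests two-sided: "All analyses will be 2-sided and a significance level of" 0.05.

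No SD of daily MVPA, no control-group proportion and no conversion from an odds ratio to minutes is given.

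**The concern.** A trial that compares mean minutes per day is sized from a difference in means and an SD. The inputs printed here are an odds ratio for a yes/no outcome and a number derived from it in some unstated way, while the conclusion is about minutes. Nothing in the text links the two.

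This is the power claim for the primary outcome, and it appears in two sections without qualification. If it has no valid basis, readers and the investigators do not know what size of effect the trial was built to find.

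**Working it through.** **Inputs from the article.** Two-sided alpha 0.05 (z = 1.960), power 0.80 (z = 0.842), 1:1 allocation, 10% dropout, OR 2.74 (95% CI 2.01 to 3.75), delta −1.37, claimed difference 5 min/day, 42 per group. Evaluable children per group: 42 × 0.9 = 37.8, about 38.

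**1. What is 1.37?**
- Difference of the OR from the null: 2.74 − 1 = 1.74.
- Log OR: ln(2.74) = 1.008.
- Half the OR: 2.74 / 2 = 1.37, an exact numerical match.

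The label on delta fits neither of the first two quantities. The third is not an effect measure used for sample size.

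**2. Can 42 per group be reproduced?** Dropout is applied as n / 0.9.
- *OR 2.74 as two proportions.* p1 = odds0 × 2.74 / (1 + odds0 × 2.74), and n = [1.960√(2p̄(1−p̄)) + 0.842√(p0(1−p0) + p1(1−p1))]² / (p1−p0)². At a control proportion of 0.4, p1 = 0.646 and n = 63.4, so 64 per group before dropout and 72 after. This is the most favourable region. At 0.1 the figure is 122 before dropout, and at 0.7 it is 98. An unpooled variance lowers the minimum only to about 61, or 68 after dropout.
- *OR 2.74 as a standardised difference.* d = 1.008 × √3 / π = 0.556. The t-test needs 52 per group before dropout and 58 after.
- *1.37 as a standardised difference.* n = 9.4 before dropout, and 9.4 / 0.9 = 10.5, about 10 to 11 after.
- *1.37 as an OR.* At least 636 per group before dropout.
- *5 min as a mean difference.* Not computable without an SD.

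Two routes come close:
- The upper confidence limit, OR 3.75, gives 37.7 / 0.9 = 41.9 at a control proportion of 0.3, and 38.0 / 0.9 = 42.2 at 0.4. The article states no control proportion and does not say that the upper limit was used.
- A one-sided test on d = 0.556 without dropout gives 41. That contradicts the stated two-sided testing and the dropout allowance.

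**3. What can the stated number detect?** By the normal approximation, d = (1.960 + 0.842) × √(2/37.8) = 0.644. The t-test gives 0.653.
- 84 randomised (37.8 evaluable per arm): 0.65 SD, so 5 min needs SD ≤ 5 / 0.653 = 7.66 min.
- 80 randomised (40 × 0.9 = 36 per arm): 0.67 SD, so SD ≤ 5 / 0.670 = 7.5 min.
- With adjustment for one baseline value at an assumed correlation r, the raw SD may be 7.66 / √(1−r²): 7.66 / 0.866 = 8.8 min at r = 0.5, and 7.66 / 0.714 = 10.7 min at r = 0.7.

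**4. Power for 5 min over a range of SDs.** The SDs are assumptions, because the article gives none. The test is an unadjusted two-sided t-test with 38 per arm. The last column is 0.653 × SD.

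| Assumed SD (min/day) | Power for 5 min | Difference detectable at 80% power (min/day) |
|---|---|---|
| 10 | 58% | 6.5 |
| 15 | 30% | 9.8 |
| 20 | 19% | 13.1 |
| 25 | 14% | 16.3 |

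**The case against.** The strongest defence is that this is a journal article, and a fuller protocol or analysis plan may hold the SD. That stands as far as it goes: the missing SD alone would be a weak point. It does not rescue what is printed. An added SD would not turn an odds ratio for a proportion, or a delta that does not match its own label, into a basis for a difference in minutes.

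Second, the planned analysis is a mixed model over three time points, with a GEE approach to control baseline differences. It may be more efficient than an unadjusted t-test. This also stands, and it is why the power figures above are only illustrative.

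A reader might also infer more than the article supports:
- *That the trial is underpowered for 5 min.* No SD is documented. At about 7.7 min or less, or at a somewhat larger raw SD with baseline adjustment, the planned number would suffice.
- *That delta was obtained by halving the OR.* The arithmetic matches exactly, but the article does not say so.
- *That the minus sign shows an error.* Control minus intervention would give a negative sign for a benefit, and the claimed difference is written as ±.
- *That no printed number can lead to 42.* The upper confidence limit can, once a control proportion is assumed.
- *That a null result will be taken to exclude a 5 min effect.* The article does not commit to that reading, and a confidence interval would settle it.

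**Conclusion.** The point holds as a mismatch of effect scale. The trial's primary endpoint is a mean, the printed inputs are for a proportion, and delta is undefined. From those inputs, under the stated error rates and dropout, 42 per group cannot be reproduced without an unstated assumption. The direct readings give 68 to 72 or more (two proportions), about 58 (converted OR) or about 10 to 11 (1.37 as a standardised difference). The ±5 min claim is therefore unsupported rather than disproved.

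What can be said firmly is that 80% power corresponds to about 0.65 SD with 84 randomised, or 0.67 SD with 80, for an unadjusted comparison after 10% dropout. Whether that equals 5 min depends on an SD, and possibly a baseline correlation, that the article does not state.

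**What to change.** - Remove the odds ratio and the delta of minus 1.37 from the Sample size section.
- Reconcile the planned number. The abstract, the eligibility section and the captions of Figs. 1 and 3 say 80 (the captions giving 40 per group). The Sample size and Sequence generation sections say 42 per group and 84.
- Restate the calculation for a difference in mean daily MVPA, with an explicit SD and its source. One source is the pooled SD from the baseline accelerometry, computed without reference to arm. Recruitment had already started, so these data need no unblinding.
- If baseline adjustment is credited, state the correlation and match it to the planned model. The factor √(1−r²) used above is for a single follow-up value adjusted for baseline.
- In both the Primary outcome and Sample size sections, replace ±5 min with the difference detectable at 80% power for the reconciled number, or keep 5 min and state the actual power.

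The cost is a short recalculation and the rewording of these sections. No additional children are needed. Whether the restated detectable difference is larger or smaller than 5 min depends on the SD found.

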## Assignment of interventions: allocation

### Sequence generation {16a}

Eligible participants will be randomly assigned to one of two groups using a computer-generated block randomization schedule (Research Randomizer V.4). Assignment will take place through previously constructed balanced blocks, which will allow equiprobable assignment and ensure that each group has the same number of participants. This allocation mechanism will be carried out until 84 total participants are assigned.

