**Methods/design:**

A total of 80 children, aged 4 to 5 years old, will be randomly assigned in a 1:1 ratio to one of two groups: the exercise group and the routine care group. The exercise group will undergo a 12-week exercise intervention, followed by a 12-week follow-up period. On the other hand, the routine care group will undergo a 12-week period of routine care, followed by a 12-week follow-up control period. The exercise program will be implemented in a family setting and facilitated through a gamified web platform with online supervision, with the hypothesis that it will have a positive impact on physical fitness, anthropometric measures, basic motor competencies, and adherence to 24-h movement guidelines.

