### Eligibility criteria {10} and recruitment {15}

A total of 80 children of both sexes between the ages of 4 to 5 years old will be recruited from the “Iturrama Primary Care” (Pamplona, Navarra, Spain). Participants will be admitted if their parent(s)/guardian(s) have provided informed consent for their participation in the project and if, according to their pediatrician, they do not have physical or mental disorders that would prevent them from completing the assessment tests or participating in the exercises provided in the intervention program. It is a requirement to have at least one parent/guardian answer the questionnaires included in the protocol. Participants (children) who at the start of the project present a psychiatric disorder or chronic illness that limits their participation in physical activities, those who do not comply with the established procedures, and those who do not understand the Spanish language will be excluded from the study.

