**Fig. 1 Fig1:**
[figure not shown]
Flow of subjects through the “3, 2, 1 Move on Study.” Participants will be first randomly assigned to a 12-week period of standard daily routines (*n* = 40) or exercise training (*n* = 40). Both groups will be included in a 12-week follow-up period

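### The protocol gives two unreconciled enrolment targets: 84 children (42 per group) and 80 children (40 per group)

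*Protocol article*

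**What the plan says.** Two sections of the protocol article set the trial at 84. Sample size {14}, after allowing for 10% dropout, concludes that "42 participants per group will be needed for sufficient power". Sequence generation {16a} carries that into conduct: "This allocation mechanism will be carried out until 84 total participants are assigned".

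Three places set the whole trial at 80:

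- The methods part of the abstract states: "A total of 80 children, aged 4 to 5 years old, will be randomly assigned in a 1:1 ratio".
- The section on eligibility (item 10) and recruitment (item 15) opens with: "A total of 80 children of both sexes between the ages of 4 to 5 years old will be recruited".
- Fig. 1 caption, on random assignment: "standard daily routines (*n* = 40) or exercise training (*n* = 40".

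The Fig. 3 caption also gives 40 per group and 80 in all, but as the explanation of a double-asterisk marker that denotes "a random subsample of participants (40 subjects in each group". The figure itself is not shown, so what the marker is attached to is unknown.

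**The concern.** The target number decides when recruitment ends, whether the allocation schedule is completed, and how many children the intention-to-treat population should contain. With two totals in current text, stopping at 80 and stopping at 84 could each be reported as going to plan, and a reader of the results could not tell whether the trial reached its target. Trial status says that recruitment was already under way, so the ambiguity touches conduct as well as wording.

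The lower total also falls short of the number that the protocol says it needs. If 80 is the true target, the power statement was written for a larger trial than the one being run.

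**Working it through.** **Inputs from the article.** 42 per group after 10% dropout, alpha 0.05, power 0.80 and a between-group difference of 5 min in mean daily MVPA (Sample size). Allocation to 84 (Sequence generation). 80 in total, 1:1 (abstract). 80 recruited (eligibility). 40 + 40 randomised (Fig. 1). Two-sided testing (Statistical methods).

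**1. The totals.**
- 2 × 42 = 84, so Sample size and Sequence generation agree with each other.
- 2 × 40 = 80, so the abstract, eligibility section and Fig. 1 agree with each other.
- The gap is 84 − 80 = 4 children, 2 per group, and 4/84 = 4.8%.

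**2. Can one total be derived from the other?**
- 80 as completers out of 84: 84 × 0.9 = 75.6, not 80. The three places that give 80 also attach it to recruitment or random assignment, not to completion.
- 84 as 80 inflated for dropout: 80/0.9 = 88.9, not 84. The 42 per group already includes the dropout allowance.

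Neither route works.

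**3. Can the 42 per group be reproduced?** Not from the stated inputs. The article gives no standard deviation (SD) for MVPA and no control proportion.
- An odds ratio of 2.74, two-sided, needs at least about 64 per group before dropout over control proportions from 0.05 to 0.9.
- An odds ratio of 1.37 needs at least about 639 per group.
- A standardised difference of 1.37 needs 9 per group, or 10 with dropout.
- A 5 min difference gives 42 only if the SD is about 7.7 min (37 per group, and 37/0.9 rounds up to 42).

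**4. Illustration of the power lost.** Assume that 42 per group gives exactly 80% power for 5 min. After 10% loss, 42 × 0.9 = 37.8 and 40 × 0.9 = 36.0 per group. With the normal approximation:
- SD = 5 / [(1.960 + 0.842) × √(2/37.8)] = 7.76 min.
- Power at 36 per group = Φ(5 / [7.76 × √(2/36)] − 1.960) = Φ(0.774) = 78.1%.

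The answer does not depend on the 10% loss. The same result follows from 2.802 × √(40/42) = 2.734, less 1.960, which is again 0.774. It depends only on the assumption that 42 per group gives 80%.

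**5. Range over assumed SDs** (5 min difference, 10% loss in both cases):

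| Assumed SD (min) | Power, 42 per group | Power, 40 per group |
|---|---|---|
| 7 | 87.4% | 85.8% |
| 7.5 | 82.6% | 80.7% |
| 8 | 77.6% | 75.5% |
| 10 | 58.5% | 56.4% |

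The absolute level moves a great deal with the SD. The difference between the two totals stays at about 2 percentage points.

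**The case against.** The strongest reply is that the operative rule is the allocation rule. It runs to 84 and meets the Sample size section exactly, and the eligibility section says that 80 will be recruited without calling this a ceiling. On that reading nothing is short, and the 80s are leftover round numbers. This stands to a degree: the documents do not show that the trial will enrol too few children. It does not remove the contradiction, because the abstract and Fig. 1 also describe randomisation, and they put 80 through it.

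A reader might also infer that 80 children fail to deliver the stated 80% power on the plan's own assumptions. The documents do not support that. The 78% is back-solved from the premise that 42 per group gives exactly 80%, and the article states no SD. On the effect sizes it does state, the answer changes with the one chosen: the odds ratio of 2.74 would leave both totals short, and a standardised difference of 1.37 would leave both ample. The planned analysis also carries baseline values forward for dropouts, so 37.8 and 36.0 are not the planned denominators, although the size of the loss does not depend on them.

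Finally, Fig. 3 might be counted as a fourth statement of 80. It is a legend to a marker in an unseen figure, and it speaks of a subsample. It could mean the whole trial or 80 drawn from 84, so it cannot be used as evidence for either total.

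**Conclusion.** The contradiction is certain and rests on the article alone: 84 in two sections, 80 in three other places, and no arithmetic or text that connects them. One set is wrong as written. If recruitment ends at 80, the trial is 4 children (4.8%) below its own stated requirement and the allocation list to 84 cannot be filled. If it ends at 84, the requirement is met and the abstract, eligibility section and Fig. 1 are wrong.

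The numerical effect is modest: about 2 percentage points of power, conditional on 42 per group giving exactly 80%, which the article does not allow anyone to verify. Whether 42 is itself adequate is a separate question. The reason to act is that a core design number should have one value.

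**What to change.** State one total everywhere. There are two ways to do it:

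- **Use 84.** Change 80 to 84 in the abstract and the eligibility and recruitment section, and 40 to 42 per group in Fig. 1. Sample size and Sequence generation then stay as they are. This is a text correction, but it means four more children if recruitment was in fact organised around 80.
- **Keep 80.** Change 84 to 80 in Sequence generation. In Sample size and Primary outcome, restate the power or detectable difference for 40 per group, recomputed from a stated SD of daily MVPA with its source. This needs no extra children. The 78% above should not be copied into the protocol, because it rests on an assumption and not on a stated SD.

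Under either option, say in the Fig. 3 note whether the 80 is the whole sample or a true subsample and, if the latter, which measurements it applies to and how the children are chosen.
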